#### Study design and sample size

2.3.1

We will carry out a pragmatic randomized clinical trial (type: parallel group) with patients suffering from FM to compare the effect of a multicomponent therapy with usual clinical care in PC. The intervention will be structured in study units. Each study unit consists of a MT group and a control group, each with 10 to 12 participants. Assuming an alpha error of 0.05 and a beta error of 0.05 in a bilateral contrast, and an estimated dropout rate of 20%, a sample size of 130 participants in each group of the study will be required in order to detect a score difference equal or higher than 5 units in the Short Form 36 (SF-36) health survey questionnaire. A common standard deviation of 10 is assumed. Based on these calculations, we will create a total of 14 MT groups, with their respective control groups, between April and December 2019. The number of participants estimated is 336 patients.

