#### Outcomes

2.3.4

The main result variable of the study is quality of life (SF-36v2).^[42,51]^ Table 1 shows the study variables, the measurement instruments and the timing of data collection. All variables will be collected for both study groups. The cost-utility variables will be collected at 2 time points: 1 year before the beginning of the study and 1 year after the beginning of the study.

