#### Statistical analysis

2.3.5

Data analysis will take place at baseline and after 3, 9, and 15 months. Intention to treat analysis will be used. The quality of data collection will be periodically monitored to minimize biases due to incomplete data. The non-response bias will be evaluated at all points of follow up. Descriptive analyses of variables will be carried out using the media (standard deviation), median (interquartile range) or frequency (percentage), depending on the distribution of variables.

For comparisons between and within the 2 study groups (intervention and control) and the study variables, the following tests will be used: Student's *t* test for independent or paired data, McNemar, Chi-square test and analysis of variance or the corresponding non-parametric tests.

To evaluate the effectiveness of the intervention at each point of follow up, we will calculate the change in scores of the SF-36 and the other questionnaires in the intervention group minus the change in the control group, and the standardized effect size (SES). The SES will be calculated as the difference of the mean of the scores of both groups divided by the combined standard deviation. To detect differences within each study group, the difference of the means between baseline and each follow up point will be calculated, and also the effect size or standardized mean response (SMR), in accordance with Kazis’ method.^[52]^ The SMR will be calculated as the mean change divided by the standard deviation of change. To evaluate the SMR and the SES we will use Cohen rule, which classifies effect size as small (0.2 to 0.5), medium (0.5 to 0.8), and large (greater than 0.8).

Finally, multiple linear regression models will be used to explore the variables associated with the percentage change [(follow-up scores minus baseline scores)/baseline scores × 100] of the scores in the SF-36 and other questionnaires. The multivariate models will include variables that might be clinically linked, and the variables statistically significant in the previous bivariate analyses. Models will be also adjusted by confounding variables. Interactions and collinearity will be evaluated.^[53]^ Statistical significance for all study tests will be set at α ≤ 0.05 and 95% CI. The statistical package IBM SPSS Statistics v.23.0.for Windows will be used.

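### The visible text names no primary SF-36v2 score, visit or between-group analysis, yet tests at 3, 9 and 15 months all run at 0.05 against a sample size for one comparison

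*Protocol article*

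**What the plan says.** Section 2.3.4 (Outcomes) defines the primary outcome by instrument: "The main result variable of the study is quality of life (SF-36v2"). The text gives no score and no visit, and sends the reader to Table 1, which is not shown.

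Section 2.3.1 (Study design and sample size) sets the error rates: "Assuming an alpha error of 0.05 and a beta error of 0.05 in a bilateral contrast". The target is "to detect a score difference equal or higher than 5 units in the Short Form 36 (SF-36) health survey questionnaire", and "A common standard deviation of 10 is assumed". With 20% dropout, "a sample size of 130 participants in each group of the study will be required". Neither a score nor a visit is attached to these figures. The planned total is 336.

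Section 2.3.5 (Statistical analysis) assesses effectiveness separately at months 3, 9 and 15, treating the SF-36 and the other questionnaires alike. It then sets one threshold: "Statistical significance for all study tests will be set at α ≤ 0.05 and 95% CI". It states no ranking of visits or scores and no adjustment. Several analyses are listed and none is called primary: t tests, analysis of variance or non-parametric equivalents; the between-group difference in change with a standardized effect size; and linear regression of percentage change. The Abstract assigns the effect-size assessment to multiple linear regression, whereas section 2.3.5 uses regression to explore associated variables.

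**The concern.** A sample size with 5% two-sided error and 95% power describes one test. The analysis section describes at least three tests of the main outcome, one per visit, and more if more than one SF-36 score or more than one analysis is used. With no test singled out and each run at 0.05, the chance of some false positive on the main outcome exceeds the planned 5%. The choice of which result to present as the main one also stays open until the data are seen.

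The visits are not interchangeable either. Month 3 follows a 12-week programme directly, while months 9 and 15 ask about persistence. Section 2.5 also undertakes to invite controls to the next therapy group at their centre and states no timing relative to those later visits.

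The same gap affects the effect size. Five units with SD 10 can be judged only once the score is known.

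**Working it through.** **1. The plan's own figure.** Inputs from section 2.3.1: difference 5, SD 10, two-sided alpha 0.05, power 0.95, equal arms, dropout 20%.

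n per arm = 2 × (1.960 + 1.645)² × 10² / 5² = 2 × 12.995 × 4 = 103.96, so 104 evaluable. Enrolled: 104 / (1 − 0.20) = 130. This reproduces the stated 130 exactly, for one two-group comparison of one score at one time.

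**2. Chance of at least one false positive.** For k independent tests at 0.05 it is 1 − 0.95^k:

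- one score × 3 visits: 1 − 0.95³ = 14.3%
- two scores × 3 visits: 1 − 0.95⁶ = 26.5%
- ten scores × 3 visits: 1 − 0.95³⁰ = 78.5%

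Scores and visits from the same patients are correlated, so two-sided z tests were also simulated under no effect (400,000 draws). A common correlation r was used between visits and, where there are several scores, between scores; a different score at a different visit has correlation r × r. The number of scores and the values of r are assumptions.

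| Scores × visits | r = 0 | r = 0.3 | r = 0.5 | r = 0.7 | r = 0.8 |
|---|---|---|---|---|---|
| 1 × 3 | 14.3% | 13.6% | 12.5% | 11.0% | 9.8% |
| 2 × 3 | 26.5% | 24.6% | 22.0% | 17.7% | 14.9% |
| 8 × 3 | 70.8% | 63.7% | 52.7% | 37.1% | 28.3% |
| 10 × 3 | 78.5% | 70.9% | 58.6% | 41.0% | 30.7% |

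Only the first row avoids assuming how many SF-36 scores are tested. Its mildest entry, 9.8%, is about twice the planned 5%.

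**3. Power if the error rate is controlled.** The planned 336 patients are 168 per arm (14 × 12); after 20% dropout, 168 × 0.8 = 134.4, taken as 134. Power = Φ(5 / (10 × √(2/134)) − z) = Φ(4.093 − z):

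- one test at 0.05: Φ(4.093 − 1.960) = 98.4%
- each of two tests at 0.025: Φ(4.093 − 2.241) = 96.8%
- each of three tests at 0.0167: Φ(4.093 − 2.394) = 95.5%
- each of six tests at 0.0083: 92.7%

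These are Bonferroni levels. Holm rejects whatever Bonferroni rejects, so they are lower bounds for Holm. For 95% power per test, the enrolment needed per arm is 152 for two tests and 164 for three, both within 168. Six tests would need 184. The stated minimum of 130 per arm (104 evaluable) would give 91.4% for each of two tests and 88.7% for each of three. All figures treat patients as independent; clustering within therapy groups is not counted.

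**The case against.** The strongest reply is that the document is a condensed article. Table 1 and Figure 1 are not shown, a full protocol exists, and multiplicity is often left to an analysis plan. This stands in part: Table 1 may name a score, so the claim is limited to the visible text. But section 2.3.5 does not merely stay silent. It states a rule, 0.05 for all tests with effectiveness assessed at each visit, and that rule does not match the one-comparison sample size. A table of variables and timing would not by itself change it.

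Four stronger readings are tempting, and the documents support none of them:

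- **That the SF-36v2 has a fixed set of separate scores and no total, giving 24 or 30 primary tests.** The documents do not say so. Section 2.3.5 speaks of scores in the plural, which could also refer to patients and visits. The multi-score figures are therefore conditional, and their upper ends assume zero correlation, which is implausible for one questionnaire repeated in the same people.
- **That the error rate and power are meaningless.** The calculation is sound for any single comparison with SD 10. What is missing is the named comparison.
- **That the trial may declare success on any one significant result.** No section defines success that way. The quoted sentence sets a threshold.
- **That SD 10 is wrong and true power far lower.** The documents give no SD for any particular score, so a power loss from a larger SD cannot be asserted. They show only that SD 10 is not tied to a score.

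**Conclusion.** The point holds in limited form. The visible text designates no primary SF-36v2 score, visit or between-group analysis, and the stated testing rule does not deliver the 5% error rate on which the sample size rests. The size closest to the text is about 10-14% for one score at three unranked visits, with correlation assumed between 0.8 and 0. If two scores are tested it is about 15-27%, and if ten, 31-79%; these rest on an assumed number of scores as well. The sample size arithmetic is correct. The remaining uncertainty is whether Table 1 already names a score.

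**What to change.** In sections 2.3.4 and 2.3.5, name one SF-36v2 score, one visit and one between-group test as primary, at two-sided 0.05. In section 2.3.1, tie the 5-unit difference and SD 10 to that score and visit. Label all other scores, visits, questionnaires and analyses secondary, reported with confidence intervals and without confirmatory claims. Bring the Abstract's description of the analysis into line. If Table 1 already names a score, repeat it in the text.

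The choice belongs to the sponsor. A component summary at 3 months is one possibility, and the documents do not favour it over others. If more than one score or visit must count, test them with Holm and say which are in the family.

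The cost is about one paragraph and no extra patients for up to three tests: 98.4% power for one, at least 96.8% each for two and at least 95.5% each for three, under the plan's assumptions and before clustering. Two scores at three visits would drop to about 92.7% per test at the Bonferroni level. The downside is that fewer results can be called confirmatory.

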#### Economic evaluation

2.3.6

The perspective of the National Health System will be used for the analysis of the economic evaluation. The use of resources and their respective costs for both groups will be described and compared. Temporal horizon will be 12 months, with a discount rate of 3%. Costs will be calculated according to the most recent official prices published in the *Diari Oficial de la Generalitat de Catalunya* (DOGC)^[54]^ for the public sector, updated to 2019. The utilities will be calculated using the SF-36v2, to obtain the quality-adjusted life years (QALYs) as effectiveness measure. The incremental ratio of the cost-utility will be calculated dividing the difference in total mean costs in both groups by the differences in QALYs. To check robustness of results we will carry out a sensitivity analysis with various discount rates and different costs. Table 1 shows costs-related variables, measurement instruments and timing of data collection.

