**Figure 2 F2:**
[figure not shown]
Content of the multicomponent therapy sessions.

Patients in the control and MT groups will receive an appointment to attend their PCC at 3, 9, and 15 months after the beginning of the study. During these appointments they will be asked to respond to the study questionnaires (SF-36, FIQR, VAS, tender points and HADS).

All data will be collected in a software application that has been custom designed for the treatment protocol of FM in the study sites. This application will be available in the *Terres de l’Ebre* ICS website and will be linked to the electronic medical records. The application aims to standardize all information related to patients with FM who visit the USCSS and will be used for research and for clinical care.

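### The SF-36 utility schedule does not match the 12-month cost window, the discount-rate check is close to uninformative over one year, and the cost-utility ratio has no stated baseline correction

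*Protocol article*

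**What the plan says.** Section 2.3.6 (Economic evaluation) of the protocol article fixes the window and the rate: "Temporal horizon will be 12 months, with a discount rate of 3" per cent. On the outcome it says: "The utilities will be calculated using the SF-36v2, to obtain the quality-adjusted life years (QALYs) as effectiveness measure". The incremental ratio is the between-group difference in total mean costs divided by the between-group difference in QALYs. For robustness, "we will carry out a sensitivity analysis with various discount rates and different costs".

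Section 2.3.4 (Outcomes) says: "The cost-utility variables will be collected at 2 time points: 1 year before the beginning of the study and 1 year after" the start.

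Section 2.3.2 has patients complete the SF-36v2 at the first interview. The text after Figure 2 then gives both groups "an appointment to attend their PCC at 3, 9, and 15 months after the beginning of the study", and adds: "During these appointments they will be asked to respond to the study questionnaires (SF-36, FIQR, VAS, tender points and HADS"). Section 2.3.5 sets the analyses at the same four times. Sections 2.3.4 and 2.3.6 both point to Table 1 for timing; that table was not available to this review.

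**The concern.** Costs stop at 12 months, but the instrument that supplies the utilities is not given then. The nearest visits are 3 months before and 3 months after. Unless the window is fixed, an analyst could use the SF-36 area to month 9, to month 15, or to a derived month 12, and divide the same 12-month cost difference by any of them.

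Two further features of section 2.3.6 add to this. One of the two robustness checks varies a discount rate over a single year, where discounting has almost nothing to act on. A report that the ratio was stable to the discount rate would sound reassuring and mean little. The ratio is also defined from differences in means with no stated baseline correction, whereas section 2.3.5 evaluates the questionnaires as change in one group minus change in the other. Cost-utility is a declared aim in the abstract and introduction, so the ratio will be read as a main result.

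**Working it through.** The article states no cost, utility or QALY figure, so there is none to reproduce. All utility gains below are assumptions, used to show direction and size.

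**Inputs.** Horizon 12 months and rate 3% (section 2.3.6). SF-36 at 0, 3, 9 and 15 months (sections 2.3.2 and 2.3.5), that is 0, 0.25, 0.75 and 1.25 years. Assumed between-group utility gains: 0, 0.10, 0.05 and 0.02.

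**1. Utility at month 12.** Month 12 lies midway between months 9 and 15, so linear interpolation gives (0.05 + 0.02)/2 = 0.035.

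**2. QALY gain as area under the curve (trapezoids).**
- Months 0 to 9: 0.25 × (0 + 0.10)/2 + 0.50 × (0.10 + 0.05)/2 = 0.0125 + 0.0375 = 0.0500.
- To month 12, interpolated: 0.0500 + 0.25 × (0.05 + 0.035)/2 = 0.0606.
- To month 15: 0.0500 + 0.50 × (0.05 + 0.02)/2 = 0.0675.
- 0.0675/0.0606 = 1.11. With 12-month costs the QALY gain is overstated by about 11%, and the ratio is 0.0606/0.0675 = 0.90 of its matched value.
- Month-9 value carried to month 12: 0.0500 + 0.25 × 0.05 = 0.0625, or 3% above 0.0606.
- Month-15 value treated as month 12: 0.0500 + 0.25 × (0.05 + 0.02)/2 = 0.0588, or 3% below.

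**3. Other assumed profiles.** Entries in the last four columns are the incremental ratio as a multiple of its value under the interpolated 12-month area, with costs held fixed.

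| Gains at 3, 9, 15 months | 12-month area | 9-month area used | 15-month area used | Month 9 carried to 12 | Month 15 treated as 12 |
|---|---|---|---|---|---|
| 0.06, 0.06, 0.06 | 0.0525 | 1.40 | 0.78 | 1.00 | 1.00 |
| 0.08, 0.04, 0 | 0.0475 | 1.19 | 0.95 | 0.95 | 1.06 |
| 0.02, 0.05, 0.08 | 0.0344 | 1.72 | 0.65 | 1.06 | 0.95 |
| 0.06, 0.06, 0 | 0.0488 | 1.30 | 0.93 | 0.93 | 1.08 |

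The wrong window moves the ratio from 0.65 to 1.72 times. Conventions that keep to 12 months agree exactly for a sustained gain and differ by about 5 to 8% in the other three profiles.

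**4. Discounting.** With one annual factor k on both parts, (k × ΔC)/(k × ΔE) = ΔC/ΔE, so the ratio does not move at any rate. With continuous within-year discounting, weight (1 + r)^(−t), the multiples over the four profiles in step 3 are:

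| Rate | Costs spread evenly over the year | Costs in the first 12 weeks |
|---|---|---|
| 3% | 0.9991 to 1.0045 | 1.0105 to 1.0160 |
| 6% | 0.9983 to 1.0090 | 1.0207 to 1.0317 |

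Applying a year-end factor to QALYs alone would move the ratio by the rate itself (1.03 at 3%, 1.06 at 6%), but nothing in the article suggests one-sided discounting.

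**5. Baseline utility.** A chance baseline difference b that has vanished by month 3 adds 0.25 × b/2 = 0.125b to the QALY difference. If it persists for the year it adds 1.00 × b. The change-minus-change calculation in section 2.3.5 removes a persisting difference from the questionnaire comparisons. Section 2.3.6 states nothing equivalent for QALYs or costs.

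**The case against.** The case for the plan has real weight.

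- **A 12-month QALY is not out of reach.** A reader might infer that, with no SF-36 at month 12, it cannot be estimated. The schedule does not support that: months 9 and 15 bracket month 12, and conventions that respect the horizon differ little.
- **The sensitivity analysis is not empty.** A reader might infer that it cannot move the result. Section 2.3.6 also varies costs, and that can. Only the discount-rate half is close to inert, and a redundant rate does not itself introduce bias.
- **Section 2.3.4 probably describes resource use and costs.** Patients cannot answer a questionnaire a year before they enrol. A reader might take it as a two-point utility schedule. On the first set of assumed gains that would give (0 + 0.035)/2 = 0.0175 QALYs against 0.0606, about 3.5 times smaller. The article does not propose discarding the 3- and 9-month data, so this is not a consequence of the plan. Table 1 may settle the wording.
- **The silence on sampling error is not a planning error.** A reader might conclude that the ratio will carry no measure of uncertainty. This is a condensed article, and bootstrap or acceptability-curve detail is commonly left to the full protocol or analysis plan.

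What remains is what the text does state: a 12-month horizon beside a utility schedule without month 12, a discount rate and its variation chosen for a one-year analysis, and a ratio defined from differences in means although the data for a baseline correction are collected.

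**Conclusion.** The point holds in limited form. The cost window and the utility schedule are misaligned as written, and the article gives no rule that joins them. If a 15-month QALY area were paired with 12-month costs, the QALY gain would be overstated by about 11% under the first set of assumed gains; across the other four profiles, a 9- or 15-month area puts the ratio at 0.65 to 1.72 times its matched value. These sizes rest on assumed utilities, and the article does not say that either wrong window will be used. Once 12 months is respected, the remaining choice of convention matters by about 8% at most in these examples.

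The discount-rate finding is firmer: no change under a common factor, and at most about 3% at rates up to 6% when both costs and QALYs are discounted within the year. Varying costs is therefore the only informative robustness check named. The baseline point rests on what section 2.3.6 states; a fuller document may add the adjustment.

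**What to change.** - Keep the 12-month horizon. Define QALYs as the area under the 0, 3, 9 and 15-month utility curve cut at month 12, with the month-12 value interpolated linearly between months 9 and 15. Count costs over the same 12 months.
- State in section 2.3.4 that the two time points refer to resource use and costs, and that utilities follow the SF-36 visits.
- Delete the discount rate and the sensitivity analysis that varies it. Keep the variation in costs.
- Estimate incremental QALYs adjusted for baseline utility, and incremental costs adjusted for prior-year costs. Both covariates come from data the plan already collects.
- Put bootstrapped cost-QALY pairs in place of the discount-rate check, so that a named check reflects sampling error.

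The cost is revised wording and a little more analysis work. No added visit, questionnaire or data extraction is needed.

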#### Randomization, recruitment, and data collection

2.3.2

For each study unit a randomization list will be generated according to Efron procedure,^[41]^ using the IBM SPSS Statistics v.23.0. package for Windows. An appointment will be arranged with patients who meet inclusion criteria for the first interview, where they will receive the information leaflet of the study and will sign the informed consent form. Next, patients will be allocated to a study group according to the randomization list. Additionally, the patients will be asked to respond to the study questionnaires (SF-36v2 health survey questionnaire^[42]^ (Optum, Inc. license number QM048943), Revised Fibromyalgia Impact Questionnaire (FIQR),^[43,44]^ Visual Analog Scale (VAS),^[45,46]^ tender points^[47]^ and Hospital Anxiety and Depression Scale (HADS)^[48,49]^) and will take part in the activities planned for each group (see below).

Control group: Patients in the control group will receive regular clinical care in their PCC,^[50]^ which consists on an individual visit with the FM specialist, who will conduct a standardized clinical history and will inform the patient on the disease using a custom designed leaflet.

MT group: in addition to usual PC clinical care, participants will receive MT consisting of health education, exercise and cognitive-behavioural therapy, during 12 weeks in 2-hourly weekly sessions (Fig. 2). Group therapy will be delivered by the FM specialist in each PCC, with the support of the physiotherapist and the psychologist of the USCSS.

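### The cost-utility ratio is defined without baseline adjustment, although prior-year costs and baseline SF-36v2 utility are collected in both arms, so chance imbalance passes partly into it and precision is lost

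*Protocol article*

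**What the plan says.** All of this is in the protocol article.

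- **The ratio.** Section 2.3.6 computes it by "dividing the difference in total mean costs in both groups by the differences in QALYs". No covariate or baseline term is named. The only robustness check named there varies the discount rate and the costs.
- **Utilities and horizon.** Section 2.3.6: "The utilities will be calculated using the SF-36v2, to obtain the quality-adjusted life years (QALYs) as effectiveness measure", and "Temporal horizon will be 12 months, with a discount rate of 3" per cent.
- **Cost data.** Under section 2.3.4, the cost-utility variables are "collected at 2 time points: 1 year before the beginning of the study and 1 year after the beginning of the study". The same section says: "All variables will be collected for both study groups".
- **Baseline utility.** Section 2.3.2, on the first interview, after describing allocation: "Additionally, the patients will be asked to respond to the study questionnaires (SF-36v2 health survey questionnaire" and the other instruments.
- **Follow-up.** Patients in both groups "will receive an appointment to attend their PCC at 3, 9, and 15 months after the beginning of the study".
- **Contrast.** Section 2.3.5 compares questionnaire scores as net change from baseline between arms and describes regression models with confounder adjustment. Both concern questionnaire scores. Neither is extended to costs or QALYs.

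**The concern.** A QALY computed as the area under the utility curve begins at baseline utility, so a gap between arms at entry is part of the outcome. Baseline utility also predicts later utility, which carries the gap forward. Costs behave similarly: patients who used many resources in the year before the study tend to do so in the year after. A formula with no baseline term lets chance differences at entry move both numerator and denominator.

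Cost-utility is a stated objective of the trial, and the ratio has a small denominator, so a shift of a few hundredths of a QALY changes the cost per QALY noticeably. The two covariates that would remove most of this are already being collected. The same instrument, the SF-36v2, is corrected for its baseline when it measures effectiveness but not, as written, when it supplies utilities.

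**Working it through.** **Sample size, to fix the number per arm.** Inputs from section 2.3.1: two-sided alpha 0.05, beta 0.05, difference 5, SD 10, dropout 20%.

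n = 2 x (1.960 + 1.645)^2 x 10^2 / 5^2 = 104 per arm; 104 / 0.8 = 130. The stated 130 reproduces. The planned total also does: 14 units x 2 groups x 12 = 336, or 168 per arm.

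**Weight of a baseline gap in the QALY.** Utilities are available at 0, 3, 9 and 15 months and the horizon is 12 months. I assume trapezoids, with the 12-month value interpolated between 9 and 15 months:

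- month 0: 1.5/12 = 0.125
- month 3: (1.5 + 3)/12 = 0.375
- month 9: (3 + 2.25)/12 = 0.4375
- month 15: 0.75/12 = 0.0625

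The weights sum to 1. If utility has the same SD at each visit and each follow-up correlates rho with baseline, a baseline gap d shifts the expected QALY difference by d x (0.125 + 0.875 x rho). For rho = 0.4 the weight is 0.475; for rho = 0.8 it is 0.825.

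**Size of the QALY shift.** The documents give no utility SD and no correlation. Assumed: SD 0.08 to 0.20, rho 0.4 to 0.8, 130 per arm. The 95% limit of the chance baseline gap is 1.96 x SD x sqrt(2/130).

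| | SD 0.08, rho 0.4 | SD 0.20, rho 0.8 |
|---|---|---|
| 95% limit of baseline gap | 0.0195 | 0.0486 |
| Weight | 0.475 | 0.825 |
| QALY shift | 0.009 | 0.040 |
| Share of 0.12 | 8% | 33% |

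The 0.12 (interval 0.06 to 0.19) is the gain from the Spanish cost-utility study cited in the Introduction.

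These are 95% limits. The median chance gap is 0.67 standard errors, which on the same inputs gives about 0.003 to 0.014 QALY, or 3% to 12% of 0.12. With 168 per arm, the limits shrink by sqrt(130/168) = 0.88, to about 0.008 to 0.035.

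**Effect on the ratio.** With the cost difference held fixed and a true gain of 0.12, a shift of 0.009 multiplies the cost per QALY by 0.12/0.129 = 0.93 or 0.12/0.111 = 1.08. A shift of 0.040 multiplies it by 0.12/0.16 = 0.75 or 0.12/0.08 = 1.50.

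**Costs.** With equal SDs in the two years, a chance gap in prior-year cost enters the expected cost difference with weight rho. The documents give no SD for health-system costs, so I state only the precision at stake. Adjustment cuts the standard error by the fraction 1 - sqrt(1 - rho^2):

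- rho = 0.5: 1 - 0.866 = 13%
- rho = 0.7: 1 - 0.714 = 29%

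**The case against.** The strongest reply is that section 2.3.6 gives only the generic definition of an incremental ratio, which holds whether or not the two differences are adjusted. The covariates could sit in an analysis plan that is not shown. Part of this stands: the text never says that the differences are unadjusted, and that remains the plain reading of a formula. But the section does more than stay silent. It states the formula and names the robustness checks, and neither includes baseline, while section 2.3.5 confines baseline correction and adjusted models to questionnaire scores.

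Three stronger readings are tempting, and the documents do not support them.

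- **That the prior-year costs have no use at all.** This cannot be shown. Table 1 is not reproduced, and section 2.3.6 also plans a descriptive comparison of resource use that may cover the prior year. The wording "1 year before the beginning of the study and 1 year after the beginning of the study" would even fit a before-and-after cost comparison, though the text does not say that one is intended.
- **That the cost-utility result is biased.** The trial is randomised, so both differences are unbiased on average. What remains is conditional bias in an unlucky draw, and lost precision.
- **That imbalance passes in full into the ratio.** That would require a baseline gap that persists unchanged for 12 months, giving 0.0195/0.12 = 16% to 0.0486/0.12 = 41%. With rho below 1 the weights are below 1, which lowers the range to 8% to 33%, and even that is at the 95% limit.

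One further objection stands and changes the remedy. Section 2.3.2 lists the questionnaires after allocation, and section 2.3.3 says participants cannot be masked. A baseline SF-36v2 answered with the allocation known could carry a group difference caused by that knowledge. Prior-year cost precedes allocation and does not have this problem.

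**Conclusion.** The point holds as an improvement to a stated method. It is not an error that invalidates the analysis. As written, the ratio uses no baseline information, although both relevant baseline measures are collected in both arms. Chance imbalance then passes partly into the numerator and the denominator, and precision is given up.

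The sizes in the working rest on assumed utility SDs and correlations, on area-under-the-curve QALYs with the visit schedule above, and on 130 per arm. At the upper end the shift matters for a decision based on cost per QALY; at the median it is modest. An analysis plan that is not shown may already add the adjustment.

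**What to change.** In section 2.3.6:

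1. Estimate incremental cost by regression on arm, adjusted for the patient's cost in the year before the study.
2. Estimate incremental QALYs by regression on arm, adjusted for baseline SF-36v2 utility.
3. Form the ratio from the two adjusted differences, fitting the models jointly if preferred.
4. Report the unadjusted ratio as a sensitivity analysis.

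In section 2.3.2, state that the baseline SF-36v2 is completed before allocation is disclosed. Where that was not done, adjustment for baseline utility should be interpreted with caution; adjustment for prior-year cost is unaffected.

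The cost is analysis wording plus the order of steps at the first interview. No extra data, visits or patients are needed.
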